#### Staff (CF) eligibility

Female.Have at least one child, preferably <24 months.From the SA community in TH, NH or WF.Able to read and write.Fluent in English and another local language (Hindi, Bengali, Sylheti, Urdu or Tamil).Understand SA social norms, values and culture within study boroughs.Known and respected by their local community.Motivated to address issues related to infant growth and development.Able to manage a group and have some leadership qualities.

### Sample size

With communication and cultural sensitivity as key drivers of the NEON intervention, the sample size will partly depend on the coverage of ethnic and language groupings. The choice of ethnic/language groups were informed by the 2011 ONS Census^16^ and input from CFs stressing that, while language is important for communication, people’s practices are embedded in different ethnicities.

The main ethnic/language group(s) identified are: one group in TH (Bangladeshi/Bengali and Sylleti); four groups in NH (Indian/Gujrati, Indian/Punjabi, Pakistani/Urdu and Sri Lankan/Tamil); three groups in WF (Indian/Punjabi, Pakistani/Urdu, Sri Lankan/Tamil). In each borough, one women’s group PLA cycle will run per ethnic/language group per ward.

We aim to run 20–32 women’s group PLA cycle (with equal numbers of face-to-face and online PLA groups) at 6–8 participants per PLA group. Including control groups totals to 288–384 participants. Assuming an 80% recruitment or retention rate, this enables us to be 85% confident that the true population rate will fall between 0.76% and 0.84% (precision=0.04). This was estimated using a geometric mean cluster size=16 participants, cluster size coefficient of variation =0.7 and intracluster correlation coefficient (ICC)=0.02.

### Recruitment

#### Participants

Due to the diversity of the target population, multiple recruitment methods are needed to maximise reach and minimise inequalities or non-representative samples.^18 19^ For instance, relying solely on online recruitment may be ineffective due to digital poverty. Thus, other mediums including leveraging on existing social networks (snowballing), identifying and fostering collaborations with community leaders, and creating clear and succinct recruitment materials^20^ were employed. All study promotional materials (eg, participants information sheets, posters) will be available in English and local languages. To standardise the recruitment process, we will provide the same recruitment script and study materials to all recruiters. Potential participants will contact the RA, who will confirm eligibility, consent and register them into the study.

Participant recruitment will follow three strategies with regular advice by CRs to maximise reach:

(1) Recruitment through CFs: CFs will share study materials with their network to invite eligible participants with subsequent snowballing. We will provide training to standardise CF recruitment. (2) Recruitment through HVs, GPs and Midwifery teams: HVs, GPs and midwives who have been identified based on their geographical proximity to study wards will share study materials to eligible participants. Details of those interested will be given to the RA. (3) Online recruitment: Online social media campaigns on Facebook and Instagram will be used. See online supplemental material 1 for advertisement materials. Recruitment bias will be limited due to the above-mentioned multiple channels of recruitment and all recruiters will be blinded thereby not knowing the allocation details at the time of recruitment.

10.1136/bmjopen-2022-063885.supp1Supplementary data

#### Staff

We will recruit CFs from our local stakeholders’ network. Recruitment via CFs is particularly useful for studies with underserved or traditionally hard-to-reach populations.^21^ CFs are leaders/champions in their local community who, with training and support, help improve the health and well-being of their communities. In line with NIHR’s ‘INVOLVE’ guideline, CFs will be paid £30 for each PLA meeting and additional £5 to cover travel costs for face-to-face meetings. A comprehensive manual for the CFs will be developed with PLA experts. A tool kit will be provided to support the learnings. The CFs will attend a 3-day comprehensive workshop and additional sessions will be conducted in between the eight-meeting cycle as a refresher and address any challenges. Biweekly meetings with the RA will be conducted to discuss learnings from the sessions. The CFs will be paid through vouchers for their time similar to a 0-hour contract. HV, GP and midwives would be identified and recruited by our study partners at each study ward. Payments will be supported by NHS support costs and decided with the relevant clinical lead.

### Allocation concealment and blinding

First, treatment allocation will be concealed from participants and recruiters during participant recruitment to reduce recruitment bias. After recruitment has been completed for that ethnic/language group in the borough, the RA will reveal ward allocation to participants and CFs via text or email, listing postcodes by trial arms to allow CFs to effectively organise and deliver the intervention.

Second, outcome assessors (CRs) will be blinded where possible to reduce measurement bias. This will be achieved by CRs logging the data collected onto an electronic platform that automatically links participant ID to maintain blinding. Baseline measurement of BMI will be done by HVs in each borough who will be blinded.

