### Randomisation

Randomisation of wards will be done before the recruitment by a separate member at University College London (UCL) using the Research Randomizer software for the 18 wards stratified by borough.^17^ The randomised wards will be shared with the RA at the end of recruitment. Once sufficient numbers are recruited in an ethnic/language group, the RA will assign participants to their respective arms. Recruitment will be performed by NHS personnel who will not be aware of the randomisation. CFs/CRs will be made aware of the participant allocation before the PLA sessions start to make contact and invite participants.

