#### Secondary outcomes

##### Proposed outcomes for the definitive trial

All other individual-level, cluster-level and economic outcome measures proposed for the definitive trial will be assessed on the response, completion rates, acceptability and the adequacy of blinding for outcome assessors during data collection. Table 2 summarises outcome measures and data collection timing. See online supplemental material 5 for collection tools.

10.1136/bmjopen-2022-063885.supp5Supplementary data

**Table 2 T2:** Schedule of outcome assessments

Outcome	Outcome measures	Data collection	Timing			
			Baseline	Every 2 weeks (end of each PLA meeting)	14 weeks (end of PLA cycle)	6 months
Proposed primary individual-level outcome	Individual Child BMI z-score	RA, CRs	✓		✓	✓
Proposed secondary individual-level outcome	Children feeding behaviour*	RA, CRs	✓		✓	✓
	Parental feeding style*	RA, CRs	✓		✓	✓
	Audio/video recording of child eating behaviours and parental feeding practices	RA	✓		✓	✓
	4-day food diary†	RA, CRs	✓		✓	✓
	Network diffusion†‡	RA, CRs	✓			✓
Proposed secondary cluster-level outcome	Children’s development performance	RA, CRs		✓		✓
	Level of dental caries	RA	✓			✓
	GP healthcare utilisation	RA	✓			✓
Economic outcome	Cost tool	RA	✓			✓
	Partners time questionnaire	RA				✓
Process outcome‡	Participants feedback*	RA, CRs		✓		
	PLA cycle meeting register*	RA, CRs		✓		
	Direct observation	RA, CRs		✓		
	Sustainability assessment	RA, CRs		✓		

*The study will have to meet the Definite Go criteria in order for the study to be feasible and to be able to proceed. However, if any one of the Definite Stop criteria is met then the study stops. The ‘Go/Stop’ indicates that it is either feasible or not feasible to proceed to a definitive trial. The progression rules have been approved by the steering and data management team. Should any of the progression rules not be met, assessments and adjustments of the NEON pilot feasibility RCT will be negotiated before proceeding to a definitive trial.

†Community Facilitators will assist in administering or completing these data collection tools before sending them to RA/CRs during the intervention period.

‡For intervention groups only.

BMI, body mass index; CR, community researchers; GP, general practitioner; NEON, Nurture Early for Optimal Nutrition; PLA, Participatory Learning and Action; RA, research assistant; RCT, randomised controlled trial.

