#### Secondary individual-level outcomes

Children’s feeding behaviour will be measured using six of eight domains adapted from the validated Children’s Eating Behaviour Questionnaire deemed suitable for infants: food responsiveness; enjoyment of food; emotional overeating; desire to drink; satiety responsiveness; slowness in eating; emotional undereating; and food fussiness.^7 8 22^ Obesity risk could be linked with external eating, emotional overeating and food fussiness.^7^Parental feeding style will be assessed with a validated self-reported Parental Feeding Style Questionnaire with four scales: emotional feeding; instrumental feeding; encouragement to eat and control overeating.^23^Audio/video recording of child eating behaviour and parental feeding practices^24^ involves asking participants about the meal (eg, name, ingredients) and creating annotations that link to behaviour codes identified from NEON formative study.^25^ Before-and-after audio/video recordings will be thematically analysed using Elan Software^26^ to measure intervention effect.Child food intake: The 4-day food diary^7^ is a self-reported, prospective, open-ended survey that collects detailed quantitative estimates of food consumption of infants between 4 and 18 months.^6^ It assesses nutrient intake (eg, total fat, total carbohydrate, salt, sugar) by comparing with age-specific/sex-specific UK dietary reference values.^27^ Dietary data will be presented by age group (eg, 4–6 months, 7–9 months, 12–18 months).Network diffusion of study materials between participants and their communities: CRs will track the number of downloads using the eRedbook platform. Participants will also complete a questionnaire on the number of people they shared the material with, their family size, age, gender, relationship to the participant and platform used.Equality impact assessment (EIA): This trial should reflect the diversity of the target population by enabling equal access while accommodating different needs. An EIA tool will systematically assess likely effects of the intervention on people (eg, with respect to disability, gender, ethnicity, age, sexual orientation, religion/belief), mitigate adverse impacts and identify active steps to address existing disadvantage and promote equality.

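### Allocation is released when a group's recruitment is complete, with no condition that baseline is complete, so mother-reported and mother-enacted baseline feeding measures can be collected after the arm is known

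*Protocol article*

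**What the plan says.** All references are to the protocol article.

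- **Concealment period** (Allocation concealment and blinding): "treatment allocation will be concealed from participants and recruiters during participant recruitment to reduce recruitment bias".
- **Release to mothers and community facilitators (CFs)** (same section): "After recruitment has been completed for that ethnic/language group in the borough, the RA will reveal ward allocation to participants and CFs".
- **Release to the research assistant (RA)** (Randomisation): "The randomised wards will be shared with the RA at the end of recruitment".
- **Assignment** (Randomisation): "Once sufficient numbers are recruited in an ethnic/language group, the RA will assign participants to their respective arms".
- **Release to CFs and community researchers (CRs)** (Randomisation): "CFs/CRs will be made aware of the participant allocation before the PLA sessions start to make contact and invite participants".
- **Blinding at baseline** (Allocation concealment and blinding): "Baseline measurement of BMI will be done by HVs in each borough who will be blinded". CRs, as outcome assessors, are to be blinded where possible.
- **Baseline items** (Table 2): child feeding behaviour, parental feeding style and the 4-day food diary are collected by the RA and CRs. The meal recording is collected by the RA alone. All four have a baseline tick.
- **Nature of the diary** (Secondary individual-level outcomes): it "is a self-reported, prospective, open-ended survey".
- **Network diffusion** (Table 2): it has a baseline tick and carries the footnote "For intervention groups only".

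**The concern.** In a cluster trial where participants cannot be blinded to what they receive, baseline is the one assessment that can be kept free of knowledge of allocation. That requires baseline to be closed before allocation is released. Here the stated trigger for release is a recruitment event.

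A mother told by text or email that she will join an infant-feeding group may describe or arrange her child's feeding differently from a mother told she is in usual care. If that happens before her baseline is recorded, the arms can differ at baseline because of allocation. A before-and-after comparison then starts from the wrong point. The pilot also aims to judge how adequately data collection can be blinded. A sequence that lets arm-aware baselines through would weaken that judgement and could be carried into the definitive trial.

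**Working it through.** No power or precision figure bears on this point. The check is of the order of events.

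**1. What counts as recruited.** The Recruitment section describes entry as the RA confirming eligibility, taking consent and registering the woman. Baseline assessment is not part of that description, so completed recruitment does not imply completed baseline.

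**2. What triggers release.** Two sections address it. Randomisation refers to the end of recruitment and to sufficient numbers in an ethnic/language group. Allocation concealment and blinding refers to completed recruitment of that group in the borough. Neither mentions baseline, and no minimum interval before release is given.

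**3. Where baseline sits.** Table 2 and Data collection and management say only that data are collected at baseline. Neither places it before or after release.

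**4. Who knows what once allocation is released.**

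| Baseline item | Source | Collector (Table 2) | Protection if collected after release |
|---|---|---|---|
| BMI | Measurement | RA, CRs (text: health visitors) | Blinded health visitors stated |
| Child feeding behaviour | Questionnaire | RA, CRs | Mother not blinded; RA holds the ward list |
| Parental feeding style | Self-report | RA, CRs | As above |
| 4-day food diary | Self-report, prospective | RA, CRs | As above |
| Meal recording | Enacted by mother and child | RA | As above |

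Blinding CRs where possible protects the assessor's side only. The Randomisation section also has CRs learning allocation before sessions start.

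**5. Two internal signs that the order matters.**
- The diary runs forward over 4 days. The last woman registered in a group, if the diary applies to her infant, needs at least 4 days after registration to finish it. Her registration is also what completes recruitment. Unless release is held back by at least that long, her diary is open when she learns her arm.
- Restricting a baseline network-diffusion item to intervention groups presupposes that the arm is known when the item is given, or at least when it is used.

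**6. The article's own expectation.** Sample characteristics anticipates that some later recruits may be recruited unblinded. The check planned there concerns recruitment and does not address how baseline measures are reported.

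**7. Number affected.** The size of a borough-language group can be worked out. Six wards with 6 to 8 women each gives 6 × 6 = 36 to 6 × 8 = 48. Over 1 + 4 + 3 = 8 groups this gives 8 × 36 = 288 to 8 × 48 = 384, which reproduces the stated total. The share with an open baseline at release also needs the accrual rate, the lag before release and the dates of baseline visits. The article gives none of these.

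**The case against.** The strongest reply is that this is a condensed article. Visit sequencing may sit in the full protocol or in the participant-flow figure (Figure 2), which is not shown. The article never places baseline after release. That stands as a limit: the order is permitted, not shown to be wrong. It does not dispose of the point, because the article states a trigger, and the trigger is recruitment. If another document orders events correctly, these two sections need to match it.

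A second reply is that little depends on these baselines. Feasibility and process measures are primary. The planned effect estimate is for BMI z-score, with baseline measured by blinded health visitors. The other proposed outcomes are judged on response, completion, acceptability and blinding. This largely stands, with one exception: the before-and-after meal recordings are intended to gauge intervention effect.

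A third reply is that the Table 2 footnotes are unreliable, since the asterisk note repeats the Go/Stop note from Table 1, and that a network-diffusion form could be given to everyone and used only for intervention groups. That is fair. The entry is something to reconcile and is weak evidence about when the feeding measures are taken.

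A fourth reply is that the article already admits a risk of performance and measurement bias from incomplete blinding. That admission is general and does not address baseline timing, which is avoidable.

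A reader might also infer more than the article supports:
- *That every baseline-adjusted contrast is biased.* Only a BMI z-score contrast is planned as an effect estimate, and its baseline is protected.
- *That the recruitment-bias check fails.* The summary named there is of demographics, which knowledge of arm does not change.
- *That a count can be given.* Assuming even accrual over 4 to 8 weeks and no lag, 4/56 = 7% to 4/28 = 14% of 36 to 48 women would be about 3 to 7 per group. Both assumptions lack support in the text. The diary is also described for infants of 4 to 18 months, whereas eligibility is under 24 months.

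**Conclusion.** The point holds in limited form. The stated release rule contains no baseline condition, so it allows mother-reported and mother-enacted baseline feeding measures to be collected after the arm is known. The consequence is confined to secondary feeding measures, chiefly the before-and-after recordings, and to the assessment of how adequate blinding was. The BMI z-score baseline is largely unaffected, provided health visitors measure it as the text says. Table 2 lists the RA and CRs for that measure.

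The conclusion assumes that the two sections describe the procedure actually used and that nothing unseen makes release wait for baseline. The number of women affected cannot be derived from the article. This is a cheap improvement to a badly fixed rule. It is not a threat to the pilot's primary aims.

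**What to change.** - In Randomisation and in Allocation concealment and blinding, make release of ward allocation to the RA, CFs, CRs and participants conditional on every consented woman in the group having completed, or passed a fixed closing date for, each Table 2 baseline measure.
- Record the date of release and the date each baseline measure was completed. Flag and report any baseline completed after release.
- Reconcile the network-diffusion baseline tick with its restriction to intervention groups, either by collecting the item from all arms before release or by dropping the baseline assessment.

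The cost is a wording change and a short delay between filling a group and its first session. The fixed closing date keeps that delay bounded when a few women are slow to finish.

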### Intervention

#### NEON women’s group PLA cycle

The co-adapted NEON women’s group PLA cycle tailored to ethnic/language groups will be delivered face-to-face at community/children’s centre or online over 14 weeks (1 session per 2 weeks). HVs, GP and midwives’ teams will be invited to 1–2 sessions to provide evidence-based information on participants’ request. To reduce study contamination, participants may not switch wards (ie, switch arms) after treatment allocation is revealed. Figure 3 illustrates the aim of each PLA session.

**Figure 3 F3:**
[figure not shown]
NEON Women’s Group PLA Cycle. NEON, Participatory Learning and Action; PLA, participatory learning and action.

A culturally sensitive intervention package has been codeveloped consisting of:

PLA group facilitator manual.Picture cards with recommended and non-recommended infant feeding, care and dental hygiene practices, and facilitators/barriers to uptake.Healthy baby food recipes.Community asset maps (eg, low-cost fruit/vegetable shops).List of relevant resources and services.

Online arm participants may access this toolkit through the eRedbook platform and receive NEON information the via the app or website. A logic model (online supplemental material 2) shows the relationship between these activities and resources and their intended short-term, medium-term and long-term effects.

10.1136/bmjopen-2022-063885.supp2Supplementary data

#### Control (usual care)

In all wards, HV teams have regular mandatory postnatal visits for all families of newborns and infants. These visits are immediately after birth, 6–8 weeks, 12–16 weeks, 1 year and 2–2.5 years. One optional prenatal visit is conducted by HVs between 28 and 32 weeks of pregnancy. Online supplemental material 3 lists other initiatives and resources available in each study borough as part of usual care.

10.1136/bmjopen-2022-063885.supp3Supplementary data

### Outcome

#### Primary outcomes

##### Feasibility and process outcome measures

We will collect quantitative and qualitative data to assess Go/Stop criteria (table 1) on recruitment and retention rates, intervention support, acceptability, fidelity and participant adherence using:

Study record: An enrolment log will record all eligible participants, total enrolled, reasons for non-participation, number followed up on child BMI z-score, and the date on how many people responded to adverts/invitations. Prescreen failure logs will record those eligible but not enrolled, with reasons. PLA session audio/video recordings will be collected using secured Dictaphone, video cameras, CCTV and/or Zoom recording.Process measurements: These include Participants’ Feedback Questionnaire, Facilitator’s Feedback Form, PLA Cycle Meeting Register, direct observation of intervention delivery and CF performance by CRs, and Sustainability Assessment Tool (online supplemental material 4).

10.1136/bmjopen-2022-063885.supp4Supplementary data

**Table 1 T1:** Go/Stop criteria for the definitive trial*

Definite Go	Definite Stop
≥50% of eligible participants consenting to pilot feasibility study.	<40% of eligible participants consenting to pilot feasibility trial.
≥80% of mothers attend ≥60% of planned sessions in the intervention arm.	<20% of mothers attend ≥60% of sessions as planned in each intervention arm.
Retention of ≥70% of consented participants for primary outcome data collection.	Retention of <50% of participants at 6 months.
High intervention support with respect to content, frequency, duration and quality.	Low support of intervention procedures.
Intervention is perceived as acceptable.	Intervention perceived as unacceptable.

*The study will have to meet the Definite Go criteria in order for the study to be feasible and to be able to proceed. However, if any one of the Definite Stop criteria is met then the study stops. The ‘Go/Stop’ indicates that it is either feasible or not feasible to proceed to a definitive trial. The progression rules have been approved by the steering and data management team. Should any of the progression rules not be met, assessments and adjustments of the NEON pilot feasibility RCT will be negotiated before proceeding to a definitive trial.

NEON, Nurture Early for Optimal Nutrition; RCT, randomised controlled trial.

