## Methods and analysis

### Design

This three-arm pilot feasibility cluster RCT study is expected to run from July 2021 to May 2023 in three East London boroughs. Eighteen clusters defined as borough wards will be randomised with 1:1:1 allocation to two intervention arms (face-to-face or online NEON women’s group PLA cycle) and one control arm (usual care). An online arm enables the trial to continue under COVID-19 restrictions; usual care was selected as control to avoid depriving participants of essential and available infant and maternal care services. Multilingual CFs will deliver interventions in respective ethnic/language groups. Ward-level randomisation is a trade-off between minimising contamination and ensuring maximum SA population representation given the diversity in the ethnic makeup, that is, SA subgroups, of the aforementioned boroughs.

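### The recruitment row of the Go/Stop table scores only the consent percentage, so it can read Definite Go when too few mothers enrol to form the 20–32 PLA groups the plan aims for

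*Protocol article*

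**What the plan says.** Table 1 (Protocol article, Feasibility and process outcome measures) gives recruitment one row. Definite Go is "≥50% of eligible participants consenting to pilot feasibility study"; Definite Stop is "<40% of eligible participants consenting to pilot feasibility trial". The other rows concern session attendance, retention, support for the intervention and acceptability. The footnote requires the Go criteria to be met, stops the study if any Stop criterion is met, and provides for negotiated adjustments if a progression rule is not met.

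The volume targets are in the Sample size section: "We aim to run 20–32 women’s group PLA cycle (with equal numbers of face-to-face and online PLA groups) at 6–8 participants per PLA group", and then "Including control groups totals to 288–384 participants". One PLA cycle is planned per ethnic/language group per ward. The Randomisation section makes group formation depend on numbers: "Once sufficient numbers are recruited in an ethnic/language group, the RA will assign participants to their respective arms". Table 1 does not refer to any of these figures. The enrolment log, described just before the table, will hold the counts of eligible and enrolled mothers.

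**The concern.** The intervention is delivered in groups, so recruitment has to fill a set of ward-by-language cells with about six to eight mothers each. A consent percentage says how willing the mothers who were found are to join. It does not say whether enough were found, or whether they live in the right wards and share a language.

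The wards are the six with the highest density of Asian population in each borough, so a shortfall here would be an important warning for a definitive ward-randomised trial. The recruitment row would not record it if at least half of the eligible mothers consented. The denominator may add to the problem. Several recruitment routes rely on mothers making contact themselves, and mothers logged that way have already shown interest, so a high consent share need not mean wide reach.

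**Working it through.** **Inputs.**
- Language groups: 1 in Tower Hamlets, 4 in Newham, 3 in Waltham Forest (Sample size).
- Wards: six per borough (Setting), 18 in all, allocated 1:1:1 (Design).
- Group size: 6–8 mothers (Sample size).
- Precision inputs: rate 0.80, confidence 85%, cluster size 16, coefficient of variation 0.7, ICC 0.02 (Sample size).
- Eligible pool: not given, so assumed below over a range.

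**1. Reproduce the planned total.** Groups = (1 + 4 + 3) × 6 = 48, of which two thirds (32) are PLA and one third (16) control. 48 × 6 = 288 and 48 × 8 = 384, exactly the stated range. The Abstract speaks of 12 wards. If these were four per borough, 8 × 4 = 32 groups and 192–256 mothers would follow, which does not match, so 18 wards is used here.

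**2. Reproduce the precision.** Design effect = 1 + ((0.7² + 1) × 16 − 1) × 0.02 = 1 + 22.84 × 0.02 = 1.457. Half-width = z(0.925) × √(0.80 × 0.20 × 1.457 / N), with z(0.925) = 1.44. This gives 0.041 at N = 288 and 0.036 at N = 384, in line with the stated 0.04.

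**3. What the recruitment row allows.** Assume exactly 50% consent, enrolled mothers split across arms as the wards are (two thirds in PLA arms), and groups of six.

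| Eligible (assumed) | Enrolled | Recruitment row | In PLA arms | Full PLA groups, at most |
|---|---|---|---|---|
| 120 | 60 | Go | 40 | 6 |
| 240 | 120 | Go | 80 | 13 |
| 360 | 180 | Go | 120 | 20 |
| 576 | 288 | Go | 192 | 32 |

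The last column takes the two PLA arms together. With exactly 40 mothers in each arm, the second row would give 12. These are best cases, because they assume mothers fall neatly into ward-by-language cells, and participants may not switch wards once allocation is revealed. Twenty groups of six need 20 × 6 = 120 mothers in PLA arms, hence 120 ÷ (2/3) = 180 enrolled and 180 ÷ 0.5 = 360 eligible. At 60% consent the break-even pool is 180 ÷ 0.6 = 300.

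**4. The two lower limits.** Twenty PLA groups with a matching 10 control groups is 30 groups: 30 × 6 = 180 to 30 × 8 = 240 mothers. The stated lower total of 288 needs all 48 groups. At N = 180 the formula in step 2 gives a half-width of 0.052, not 0.04. The lower end of the group range therefore does not deliver the stated lower total or the stated precision.

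**The case against.** Four points can be made for the plan.

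First, a Go on recruitment does not release the definitive trial. A reader might infer that a badly under-enrolled pilot would be sent forward. The documents do not support that, because the footnote requires the other Go criteria as well.

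Second, the attendance row might catch a severe shortfall. Mothers whose group never forms attend nothing, and if they are counted, attendance falls and could reach Stop. This works only if those mothers stay in the denominator, which the article does not settle. It is a possible safeguard, not a stated one.

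Third, volume is recorded and reviewed. The enrolment log captures it, the steering team meets every three months, and a structured decision tool is applied before progression. All true, but neither the review nor the tool is given a numerical threshold. The footnote's negotiated adjustments depend on a rule not being met, and low volume with 50% consent does not breach the recruitment rule.

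Fourth, a proportion suits the plan's objectives, which speak of recruitment and retention rates, and the sample size is built on the precision of a rate. This stands as a reason to keep the percentage. It does not make the percentage informative about group formation.

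**Conclusion.** The point holds for the recruitment row. As written, that row can read Definite Go at any level of enrolment, and no other row counts mothers enrolled or groups formed. At 50% consent, 1:1:1 division of mothers and six per group, any eligible pool below about 360 gives Go on this row while 20 PLA groups cannot be filled. The figure is illustrative, since the article states no pool, and it shrinks as consent rises.

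Two stronger readings should be resisted. One is that the plan sets a minimum of 20 groups and then ignores it: 20–32 is worded as an aim, and the numbers that count as sufficient for assignment are not quantified. The other is that 180 mothers is the plan's own floor and could be adopted directly: the same section states 288–384, and 180 would miss the stated precision. The article fixes the progression criteria and describes them as approved, so this is not a detail left to an analysis plan. It is an inexpensive improvement to one criterion and does not invalidate the pilot.

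**What to change.** Reconcile the Sample size section first. Either the lower aim of 20 PLA groups stands, in which case the lower total is 180–240 mothers and the precision at 180 should be restated as about 0.052, or 288 stands, in which case the group aim is 32 PLA plus 16 control.

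Then keep the 50% and 40% consent limits and add to the recruitment Go cell a prespecified count: the number of PLA groups and of control groups that reach at least six consented mothers. Put a lower count in the Stop cell. The sponsor should set both numbers from the reconciled targets before the results are assessed against Table 1. It would also help to state whether mothers in groups that never form count in the attendance denominator.

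The cost is one tabulation from an enrolment log that is already planned, by ward and ethnic/language group. The downside is that the Go becomes slightly harder to reach.
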